**Methods:**

We present the aims and methods of a placebo-controlled, participant-blinded and assessor-blinded mechanistic study. Adult patients with CLBP will be randomized to receiving 16 sessions of real (active) or sham (placebo) EA over the course of 8 weeks. The primary pain regulatory measure for which the study was powered is temporal summation (TS), which approximates ascending pain facilitation. Conditioned pain modulation (CPM), representing a descending pain modulatory pathway, will be our secondary pain regulatory measure. The primary psychological measure is expectations of benefit, and the secondary psychological measures are pain catastrophizing and self-efficacy in managing pain. Main clinical outcomes are back pain bothersomeness on a 0–100 visual analog scale (primary), Roland Morris Disability Questionnaire (secondary), and relevant items from the National Institutes of Health (NIH) Patient-Reported Outcome Measures Information System (secondary). We hypothesize that compared to sham, real EA will lead to greater reduction in TS after 8 treatment sessions (4 weeks); and that reduction in TS (and secondarily, increase in CPM) after 8 treatment sessions will mediate reduction in back pain bothersomeness from baseline to week 10 (clinical response) to EA. We also hypothesize that the three psychological factors are moderators of clinical response. With 100 treatment completers, the study is designed to have 80% power to detect a medium-sized between-group effect (*d* = 0.5) on temporal summation.

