Preliminary studies in animals and healthy human subjects suggest involvement of the central pain modulatory pathway in acupuncture analgesia [32]. For example, studies by Han [33] and Pomeranz [34] independently revealed that acupuncture, particularly electroacupuncture (EA), produces pain relief by augmenting descending pain inhibition via central opioidergic receptors at the periaqueductal gray and spinal dorsal horn. Similarly, Zheng et al. showed that acupuncture reduces ascending pain facilitation, as evidenced by decreases in TS from electrical pain induced in healthy volunteers [35]. They further showed that EA produces greater reductions in TS than manual acupuncture. Most of these studies were conducted on animals or healthy volunteers [36]. In this innovative study, we propose to investigate central mechanisms of acupuncture in a clinical population suffering from CLBP.

Expectations: several clinical studies have found that pretreatment expectation of benefits from treatment is a powerful predictor of pain reduction in response to treatments [37, 38]. Sherman et al. found that expectation following initial treatment might be more relevant to eventual outcome than pretreatment expectations [39]. In the present study, we will assess expectations both after (primary) and before (secondary) the first treatment session and examine both post first-session (primary) and pre first-session (secondary) expectations as moderators of clinical outcomes.

Additional (secondary) psychological factors: some data suggest that psychological and cognitive attributes, such as perceived self-efficacy in managing pain and pain catastrophizing, may also moderate clinical outcomes in response to pain treatment in general [40, 41] and acupuncture in particular [42]. Therefore, we will assess these two constructs and examine them as moderators of clinical outcomes.

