#### Primary measures

Temporal summation (TS) - ascending pain facilitatory mechanism (primary mediator): we will use an individualized thermal TS protocol, measured on the back and the hand of each participant [50]. Through a unique participant training process and steps that aim to optimize TS by adjusting the stimulus and baseline temperatures, our method minimizes floor and ceiling effects due to variability in heat sensitivity and enables the capture of TS in a broad range of individuals [51]. This protocol delivers a series of 10 individually adjusted, supra-threshold heat pulses (0.5 s duration, given every 2 s) to the participant’s palm. TS is estimated as the difference between the rating of the second pain from the first pulse from that of the most painful pulse. We will measure TS at baseline (pretreatment measurement), during the treatment period (between the 8th and 9th treatment session), and post treatment.

Expectation of benefit - psychological mechanism (primary moderator): the Stanford Expectation of Treatment Scale (SETS) is a validated measure that assesses both positive and negative expectancies. It has a total of 6 questions (3 assessing positive and 3 negative expectations) and all questions are answered by a 7-point Likert scale scored from 1 to 7. The Cronbach’s alpha was 0.81–0.88 for positive expectancies and 0.81–0.86 for negative expectancies measured by the SETS. Participants will complete SETS both before and after the first treatment session.

Self-reported back pain bothersomeness - primary clinical outcome: participants will rate weekly back pain bothersomeness using a visual analog (VAS) 0–100 scale, where 0 is no pain and 100 is the worst pain imaginable. The back pain bothersomeness scale is specific to back pain and has been successfully used by researchers in other clinical trials [10, 52]. This measure will be collected weekly from baseline (week 0) to the post-treatment visit (around week 10).

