#### Secondary measures

Conditioned pain modulation - descending pain modulation mechanism (secondary mediator): our group has optimized and published a method to quantify CPM [51]. Briefly, we measure the change in the pain rating on application of a 30-s thermal stimulus calibrated to approximately 60/100 pain intensity of the participant, applied to his/her non-dominant hand, before and during the last 30 s of a 2-min submersion of the contralateral foot in a 10 °C water bath. The magnitude of CPM is estimated as the difference in the pain rating of the thermal stimulus before and during the cold submersion. Our previous study demonstrated that CPM measured this way is robust against cognitive influences such as reappraisal or imagery [53].

Secondary psychological moderators: we will used validated questionnaires including pain catastrophizing scales [54] and self-efficacy in pain management [55].

Secondary clinical outcome measures: these will include the Roland Morris Disability Questionnaire, which assesses physical function specific to patients with back pain, and the following PROMIS measures: pain interference, physical function, social isolation, depression, anxiety, fatigue, sleep disturbance, and sleep-related Impairment. The secondary psychological moderators and clinical outcomes will be collected in a manner identical to the QST measures at baseline, at the mid-point during treatment, and post treatment.

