#### Sample size

We computed the sample size based on detecting differential changes in TS, the primary mediator. A small pilot study conducted in our laboratory suggested an average change of 10–25 points on the 100-point VAS with a standard deviation of 12 in TS following acupuncture. Prior studies suggest no treatment effect in controls receiving sham acupuncture [35]. However, given the imprecision of the pilot study estimates of effect sizes, we have elected to power the study to detect a medium-sized effect (*d* = 0.56) with 50 subjects in each arm, using the two-tailed test with alpha = 0.05 and beta = 0.8. If the point estimates from the pilot prove to be correct, this project will be very well-powered (98% power) to detect a large effect (*d* = 0.833). To account for attrition of about 20%, we plan to enroll about 120 study participants.

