##### Planned analysis

We will use a McArthur mediation analysis strategy [60] to test this hypothesis. We will first examine if there is a significant treatment effect on the clinical outcome, testing a mixed effect model, with weekly back pain bothersomeness scores as the dependent variable and treatment assignment as the independent variable. The subject-specific intercept will be included to account for within-patient correlation. We will then test a second mixed effects model, with the longitudinally measured back pain bothersomeness scores as the independent variable. Treatment arm, reduction in TS from baseline to week 4, and their interaction will be the independent variables. A significant main effect for change in TS or an interaction between change in TS and treatment arm will be interpreted as evidence of mediation.

##### Hypothesis 2

Participants’ expectations of benefits will predict reduction in back pain bothersomeness scores during the treatment period (week 0 to week 10).

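### The hypothesis 1b mediation model leaves out the baseline predictors of pain that the trial collects, so a confounded TS–pain association can be declared mediation

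*Protocol article*

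**What the plan says.** Under Statistical methods, Hypothesis 1b, the protocol article plans two mixed models for weekly bothersomeness. The first has treatment as the only regressor. For the second: "Treatment arm, reduction in TS from baseline to week 4, and their interaction will be the independent variables". (The text there calls bothersomeness an independent variable too; I read this as a slip for dependent.) If TS reduction is significant, alone or in interaction with arm, mediation is concluded. No covariate is named, and the rule sets no direction for the effect. The Discussion presents TS-mediated relief as the trial's primary hypothesis.

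Other sections name variables that bear on the same outcome:

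- The Background reports that "pretreatment expectation of benefits from treatment is a powerful predictor of pain reduction in response to treatments". Hypothesis 2 expects expectation to predict bothersomeness in this trial.
- The Background also says that catastrophizing and self-efficacy may moderate outcome.
- The section on randomization justifies balancing the arms on baseline pain by its influence on outcome.

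All of these are available before treatment. On expectation, Primary measures says: "Participants will complete SETS both before and after the first treatment session". TS, catastrophizing, self-efficacy and CPM are measured at baseline, and bothersomeness from week 0. The psychological scales enter models of their own (hypothesis 2 and aim 3), not the 1b model.

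**The concern.** Randomization protects the comparison of arms. It does not protect the comparison, within arms, of participants whose TS fell with those whose TS did not. A baseline characteristic related both to TS change and to the level or course of pain produces a TS–pain association even when TS does nothing. Balancing the arms on baseline pain does not prevent this. The planned model has no term to absorb such a characteristic, and the decision rule turns any significant association into a statement about mechanism.

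What is at stake is the trial's main mechanistic claim. The Discussion would use a positive result to treat TS as a predictor of clinical response, and the section on clinical impact foresees its use in selecting patients.

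**Working it through.** **The plan's own figure.** The Sample size section gives power only for hypothesis 1a: "medium-sized effect (*d* = 0.56) with 50 subjects in each arm", "using the two-tailed test with alpha = 0.05 and beta = 0.8", where I read beta as power. By the normal approximation, power = Φ(d·√(n/2) − 1.96) = Φ(0.56 × 5 − 1.96) = Φ(0.84) = 0.80. The figure reproduces. No power or error rate is stated for 1b, so its behaviour has to be worked out.

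**Inputs for 1b.**
- N = 100 completers, 50 per arm (Sample size).
- Regressors: arm, TS reduction and their interaction (Hypothesis 1b, Planned analysis).
- Assumption, not in the documents: one standardised baseline factor U correlates r with TS reduction and −r with mean pain.
- Assumption: TS has no effect on pain.
- Assumption: weekly data are complete. The random-intercept test of a person-level regressor is then in effect a regression on person means.

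**Formula.** Write TS reduction as rU + √(1−r²)·e₁ and mean pain as −rU + √(1−r²)·e₂, with e₁ and e₂ independent. The induced correlation has size r². By Fisher's z, the probability of a significant result is Φ(z − 1.96) + Φ(−z − 1.96), with z = atanh(r²)·√(N − 3) = atanh(r²) × 9.85.

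- r = 0.2: r² = 0.04, z = 0.39, probability 0.059 + 0.009 = 6.8%
- r = 0.3: r² = 0.09, z = 0.89, probability 0.142 + 0.002 = 14.4%
- r = 0.4: r² = 0.16, z = 1.59, probability 0.355 = 35.5%

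**Simulation of the planned regressors** (TS main effect only, 5,000 to 8,000 trials per setting):

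| r on both paths | Planned model | With U added |
|---|---|---|
| 0.2 | 7.1% | about 5% |
| 0.3 | 14.2–14.6% | about 5% |
| 0.4 | 34.5–34.6% | about 5% |

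A direct random-intercept fit with 11 weekly ratings (250 trials per setting) gave 5.6%, 13.6% and 65.6% at r = 0, 0.3 and 0.5, and 4.4–5.6% after adjustment.

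**What changes the size.**
- *Coding of arm.* The 0.3 and 0.4 rows were checked with arm coded −0.5/+0.5. With 0/1 coding the main effect is the TS slope in one arm only, and the rates are 9.6% at 0.3 and 20.0% at 0.4. The article does not state the coding.
- *Measurement error.* If U is measured with reliability 0.7, adjustment leaves 5.7% at r = 0.3 and 14.1% at r = 0.5, against 13.6% and 69.5% unadjusted in the same runs.
- *Unmeasured U.* Nothing is gained: 14% at r = 0.3 and 71% at r = 0.5.

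**Baseline TS.** TS reduction contains baseline TS. With equal variances and test–retest correlation ρ, the two correlate √((1−ρ)/2), which is 0.59 at ρ = 0.3 and 0.39 at ρ = 0.7. If observed baseline TS itself relates to pain, this coupling adds to the problem. If only a stable TS trait matters, it adds nothing. I therefore list baseline TS as a covariate but put no separate figure on it.

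**The case against.** The strongest reply is that only half of the confounding path is documented. The article supports expectation and baseline pain as predictors of pain. It nowhere says that they, catastrophizing or self-efficacy affect thermal TS. This stands. It is why the correlations above are assumptions, and why the conclusion is that the association can be confounded, not that it is. At 0.2 on both paths the excess is only about two percentage points.

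A reader might infer that a hopeful participant who rates both heat pulses and back pain lower would be enough to produce false mediation. The documents do not support that. Primary measures defines TS as the difference between two ratings in one pulse series, so an equal downward shift cancels. Only a shift that scales with intensity would pass through.

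A reader might also take the remark that "CPM measured this way is robust against cognitive influences such as reappraisal or imagery" as an admission that TS is not robust. It says nothing about TS, and it concerns reappraisal and imagery, not expectation.

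A third reply is that covariates belong in an analysis plan, and that the article cites a published mediation strategy not shown here. This has limited force. The article prints the regressor list and the rule for reading the result, so the choice has been made and not deferred.

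Finally, the available covariates cannot remove every common cause. No measure of reporting style is described, and change in expectation during treatment is not clearly measured: Primary measures places the scale around session 1, while the Overview of measures implies a wider schedule. This also stands, and it limits what the fix can claim.

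**Conclusion.** The point holds in a limited form. The 1b model rests a conclusion of mediation on an unadjusted association with a non-randomised mediator, although baseline predictors of the outcome are at hand. With a shared baseline factor correlated 0.2, 0.3 or 0.4 with both TS change and pain, and no TS effect, the main-effect test is significant in about 7%, 14% or 35% of trials instead of 5%. These figures assume 100 completers, complete weekly data and centred arm coding, and the correlations themselves are not in the documents. Adjustment restores about 5% if the factor is measured well, and less fully if it is not.

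The stronger reading, that an expectation effect will be reported as a spinal mechanism, is not supported: neither the expectation–TS link nor its strength is given. The randomised test of 1a is unaffected. Separately, accepting either a main effect or an interaction gives about 8–10% false positives with no shared cause at all, and covariates do not cure that. I rate this point as should-fix.

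**What to change.** In the planned analysis for hypothesis 1b:

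1. Add as covariates baseline bothersomeness, baseline TS, the pre-session SETS score, baseline catastrophizing and baseline self-efficacy. Use the pre-session SETS and not the post-session score, which follows the first randomised session and may already reflect arm. The week-0 bothersomeness rating then serves as a covariate and should not also be an outcome row.
2. Base the mediation statement on this adjusted model and show the unadjusted model as supportive.
3. For CPM in aim 3, use the same list with baseline CPM in place of baseline TS.
4. Word a positive result as an association consistent with mediation, and state that unmeasured common causes, such as reporting style and change in expectation during treatment, remain.

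The cost is analysis wording only, since every variable is already collected. With 100 completers and four fixed terms, 100 − 4 = 96 person-level degrees of freedom fall to 91, or 90 if positive and negative expectancy are entered separately.

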##### Clinical impact

This clinical trial aims to delineate pain regulatory and psychological mechanisms of real (active) versus sham (placebo) EA in treating CLBP. The primary mechanisms investigated in this study are ascending pain facilitation estimated by TS, a specific measure from quantitative sensory testing, and expectations of benefit from the intervention, a psychological measure. The primary clinical outcome in this mechanistic study is back pain bothersomeness. While we will provide results on comparative efficacy of the real and sham EA in treating CLBP, our primary focus is on mechanisms and predictors of the clinical outcomes.

The results of this mechanistic study could have future clinical care implications because they will inform on the potential contribution of pain regulatory processes (mediator) and expectation of benefit (moderator) to clinical outcome. Identification of mediators of clinical response could help guide selection of patients who are most likely to respond to EA. For example, those with deficits in a given mediator variable, such as those with temporal summation deficit may potentially have better response to acupuncture. Identification of moderators will help guide decisions about targets to enhance clinical outcome. For example, we can potentially augment clinical outcome from acupuncture by an intervention to enhance expectation of benefits.

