##### Planned analysis

This hypothesis will be tested using the two-tailed, two-sample *t* test, comparing the change in TS from baseline to week 4 between the real and sham arms.

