## Discussion

We have presented an ongoing clinical trial to evaluate the mechanisms of real vs sham EA for the treatment of CLBP. Our primary hypothesis is that the reduction in subjective rating of back pain bothersomeness in response to electroacupuncture will be mediated by reduction in ascending pain facilitation, which is measured by temporal summation. Clinically, if proven true, this hypothesis would allow us to utilize temporal summation as a predictor of clinical response to acupuncture treatments, i.e. those with amplified temporal summation would have increased likelihood to achieve symptom relief with acupuncture. We also hypothesize that the clinical effects of acupuncture will be moderated by the participant’s expectation of treatment benefits, i.e., the higher the expectation, the greater the degree of reduction in back pain bothersomeness. This hypothesis may allow us to potentially increase response to acupuncture treatments by augmenting a patient’s expectation of treatment benefits.

This study utilizes novel mechanistic markers involving an array of QST measures, and examines potential psychological moderators of clinical response to acupuncture, with expectation of benefits as a primary moderator. The study is expected to yield important knowledge on the pain regulatory pathways involved in both real (active) and sham (placebo) EA treatments. The majority of the existing studies on EA in CLBP focus on efficacy alone and are often limited by a heterogeneous sample population (i.e., patients with radicular back pain due to nerve root compression or those with acute and subacute back pain are included along with those with axial CLBP), lack of controls for non-specific effects, or small sample sizes. We designed the current study to minimize these limitations. To the best of our knowledge, this is the largest placebo-controlled study to date to evaluate EA as a treatment for back pain. The QST measures we selected will offer valuable insight into the pain regulatory mechanisms of real and sham EA. The study will also provide insight on psychological measures, such as expectation, catastrophizing and self-efficacy in managing pain, as moderators of treatment response to acupuncture. These measures have been studied extensively in the pain literature but are only beginning to gather attention in the field of acupuncture research.

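### The rule for declaring mediation by temporal summation does not require that real EA changed temporal summation more than sham

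*Protocol article*

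**What the plan says.** The rule is in the protocol article, Statistical methods, Planned analysis under Hypothesis 1b.

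- The framework is named: "We will use a McArthur mediation analysis strategy [60] to test this hypothesis".
- Step one concerns pain, not TS: "We will first examine if there is a significant treatment effect on the clinical outcome". The article does not say whether the analysis stops if this test is not significant.
- Step two is a second mixed model of weekly bothersomeness: "Treatment arm, reduction in TS from baseline to week 4, and their interaction will be the independent variables".
- The decision rule follows: "A significant main effect for change in TS or an interaction between change in TS and treatment arm will be interpreted as evidence of mediation".

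The effect of treatment on TS is tested only under Hypothesis 1a, with a two-sample t test "comparing the change in TS from baseline to week 4 between the real and sham arms". Neither planned analysis refers to the other. The last sentence on statistical methods applies the same plan to Aim 3, so the rule also covers conditioned pain modulation and the secondary clinical outcomes.

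**The concern.** A real-versus-sham effect can pass through TS only if two links hold: treatment shifts TS, and TS change affects pain. The printed rule looks at the second link alone. If both arms change TS by the same amount, a TS-change main effect shows that people whose TS fell more also had less pain. A significant interaction shows that this association differs by arm. Neither shows that EA worked through TS.

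The Discussion presents mediation by TS as the trial's primary hypothesis. As the rule stands, that conclusion could be announced after hypothesis 1a has failed.

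**Working it through.** **1. The plan's own figure.** The article gives no error rate or power for the mediation rule. It does give power for the 1a test, "to detect a medium-sized effect (*d* = 0.56) with 50 subjects in each arm", two-sided alpha 0.05, with 80% power intended. The normal approximation gives 80.0% and the noncentral t gives 79.2%, so the figure reproduces. The stated 98% at d = 0.833 also reproduces (98.5–98.6%).

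**2. The indirect effect.** Write TS change as M = a0 + a·arm + error, and outcome as Y = c·arm + b·M + θ·arm·M + error. The real-versus-sham indirect effect is a·(b + θ·arm). If a = 0 it is zero whatever b and θ are. The rule tests b and θ and never a.

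**3. Inputs.** From the article: 50 per arm, equal allocation, two-sided 5%, the three model terms and the either/or rule. Assumed, because the article gives neither:
- r, the within-arm correlation of TS change with outcome, over 0 to 0.4 (0.5 for one power figure);
- the arm coding, either 0/1 or centred (±0.5).

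With balanced weekly data, a random intercept and only subject-level terms, the fixed-effect tests equal ordinary regression on subject means. The simulation therefore uses subject means, with at least 10,000 trials per scenario.

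**4. No relation at all (r = 0).** With centred coding the two tests are nearly independent, so the either/or error is 1 − 0.95² = 9.75%. Simulation gives 9.4–9.7% (centred) and 8.2–8.6% (0/1).

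**5. No arm effect on TS, but TS change and outcome correlate in both arms.**

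| assumed r | declares mediation, 0/1 coding | declares mediation, centred coding |
|---|---|---|
| 0.2 | 32% | 53% |
| 0.3 | 60% | 86% |
| 0.4 | 86% | 98% |

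Hand check at r = 0.3 for the main effect alone, by Fisher's z (atanh 0.3 = 0.3095):
- Centred coding uses all 100 people: 0.3095 × √97 = 3.05, and Φ(3.05 − 1.96) = 0.86.
- With 0/1 coding (sham = 0) the main effect is the slope among the 50 sham participants: 0.3095 × √47 = 2.12, and Φ(2.12 − 1.96) = 0.56.

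The interaction test adds its own 5% chance, which lifts the 0/1 figure to about 60%.

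**6. Step one read as a gate.** If EA affects neither TS nor pain, step one passes in about 5% of trials, so the full sequence declares mediation in about 5% or less. If EA has a purely direct effect on pain of d = 0.56, step one passes in about 79%. At r = 0.3 the product is 0.79 × 0.60 ≈ 0.47 to 0.79 × 0.86 ≈ 0.68. Simulation gives about 47% (0/1) to 67% (centred; repeat runs up to 69%).

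**7. Adding hypothesis 1a as a condition.** With a = 0, the 1a test is significant in 5% of trials, so false declarations are at most about 5% in every scenario (half that if the direction of 1a is enforced). If EA does change TS by d = 0.56, the 1a-gated rule declares mediation in about 49–67% of trials at r = 0.3 and about 78% at r = 0.5; repeat runs differ by up to 2 points. The ceiling is the roughly 80% power of the 1a test itself.

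**The case against.** **Hypothesis 1a is not absent.** It stands beside 1b under the same aim, it will be tested and reported, and a named mediation framework is cited. A careful analyst might combine the two. That is fair, but the article prints its own operational rule, and that rule does not contain the link. What is faulted is a stated rule, not detail left to an analysis plan.

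**Step one may be a gate.** The wording permits this reading, and it removes the problem when EA has no effect on pain. It does not help when EA relieves pain by another route, which is the case a mediation analysis has to distinguish.

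**The trial also studies nonspecific effects.** The section on choice of comparators says so, and an association shared by both arms is relevant to that aim. This stands in part: a zero indirect effect refers only to the real-versus-sham contrast. But there is no untreated arm, so a shared association cannot be separated from natural history or regression to the mean. Calling it mediation remains too strong.

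**Stronger readings a reader might infer.**
- *A wrong-direction effect would count.* The rule names no sign, but hypothesis 1b is itself directional, and two-sided testing of a directional hypothesis is usual. This is minor.
- *A positive result would license selecting patients on baseline TS, and the article contradicts itself on who responds.* The Clinical impact section says "those with deficits in a given mediator variable, such as those with temporal summation deficit may potentially have better response to acupuncture", and the Discussion says "those with amplified temporal summation would have increased likelihood to achieve symptom relief with acupuncture". Both are conditional commentary outside the decision rule. A deficit can loosely mean impaired regulation, which is compatible with amplified TS. The wording could be aligned, but no contradiction is shown.

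**Conclusion.** The point holds for the missing condition. As printed, mediation of the real-versus-sham effect can be declared when EA did not change TS relative to sham. If step one is not a gate, this happens in about 32–53% of trials at r = 0.2, 60–86% at r = 0.3 and 86–98% at r = 0.4. If it is a gate, the rate is about 5% or less with no effect of EA on pain, and 47–67% at r = 0.3 with a purely direct effect of d = 0.56.

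These sizes rest on an assumed r, on arm coding the article does not state, and on complete balanced weekly data. No single percentage should be quoted as the trial's error rate. That the rule omits the treatment-to-TS link depends on none of these assumptions. The documents do not support extending the point to patient selection or to a conflict between sections.

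**What to change.** Before the arms are compared, replace the either/or sentence with one governing criterion. Either would do:

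1. Declare mediation only if hypothesis 1a is met (greater TS reduction with real EA) and the relation between TS change and outcome is significant in the hypothesised direction. State the arm coding and which slope is meant, since the main effect means different things under 0/1 and centred coding.
2. Decide solely on whether the 95% confidence interval of the indirect effect excludes zero in the hypothesised direction.

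If both are reported, say which one governs. State whether step one is a gate. If hypothesis 1a fails, report TS change as a correlate of improvement in both arms, not as a mediator. Carry the same wording into Aim 3.

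The cost is wording and, for option 2, one further estimate from data already collected. The downside is that the claim becomes harder to make: with a true TS effect of d = 0.56, option 1 succeeds in about 49–67% of trials at r = 0.3 and about 78% at r = 0.5.
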